## Discussion

Rigorously produced science provides reliable information to guide clinical decisions [10, 37]. However, there is frequently a gap between scientific evidence produced and healthcare provided [12, 38], taking time [2] for the implementation of research findings into clinical practice (when it occurs) [12, 39, 40]. Besides the unpreparedness of health professionals to critically assess scientific literature for implementation in practice and to deal with it independently [34], their resistance to change, allegiance to precursor thoughts, personality traits, and beliefs [12] may contribute to this gap. It is possible that scientific evidence, which we thought was an established crucial criterion, may not be as relevant to dentists as other factors, such as treatment complexity, patient expectations, etc. Therefore, guiding evidence-based practice on the academic belief that such practice is relevant may not be the more efficient way to implement the evidence into clinical practice.

Using the methodology expected for a DCE, it is possible to capture the importance of different attributes in a group of respondents without objectively asking them which attribute they prefer. When a respondent is exposed to the experiment, the hypothetical alternatives lead him/her to choose the alternative more compatible with his/her expectations. However, if there is no ideal (perfect) alternative to him/her, he/she will mostly opt for the alternative that presents the ideal level of the most valued attribute for him/her. Considering the example given in Fig. 1, if the respondents consider cost as a very relevant aspect, they will tend to always opt for the alternative in which “low cost” (<$100) appears. They will have to opt for a second preferred option only when this option does not appear. Therefore, they do not have to say: “I prefer this or that”, but they intuitively will point out in one common direction. The repetition of this pattern will finally reflect their preference. Such a strategy has often been used to measure preferences for attributes of medical interventions, characterizing the preference by attribute importance [34].

By collecting the information using this more intuitive strategy, we believe such an assessment may reduce the choice-supportive bias on our findings. Several studies have observed that choice-supportive bias has the potential to affect future choices [41]. Previous memories, for example, related to previous knowledge of the “expected’ or “correct” answer, could influence the dentist to opt for such an expected answer (e.g., evidence-based concepts). When all attributes, including this one, are displayed together, the attribute is not in focus. Since it will be combined more naturally with the others than a unique binary question, the respondents may be more prone to not “force” non-real answers.

This study will investigate attributes that guide the choice of dental professionals in Brazil. Thus, if “non-important” attributes are valued at the expense of those who can bring decisions with greater security and benefits, future interventions can be planned to directly impact them and guide the implementation of recently produced evidence more efficiently. Bring a parallel to marketing strategies; understand the dentist as a consumer. If the marketing survey shows consumers prefer a box, no marketing strategy will consider selling a product in a bag. Coming back to evidence-based practice in health care, we should use the “appeal” that consumers or professionals are prone to adopt and customize the implementation of such evidence in clinical practice or policies.

This assessment also aims to identify possible professionals’ choice trends based on the name of the intervention rather than its characteristics. Disruptive scientific evidence may require a paradigm shift in clinical practice. Different types of cognitive bias may influence decisions and difficult changes in this process [41, 42]. Certainly, difficulties in the implementation process may result from that. Due to the reasons discussed above, the DCE may also represent an opportunity to show if the preferred (or most valued) attributes reflect the actual choice of known/traditional interventions compared to the disruptive evidence-based alternatives. Recent studies have shown that dental radiographs for detecting caries do not bring additional benefits and may cause overdiagnosis, false-positive results and lead-in time bias [43, 44]. However, it is current practice and advocated in some Pediatric Dentistry guidelines [45–47]. Depending on dentists’ allegiance or choice-supportive memories, they may resist change. This is a real example of recognizing what dentists consider in their decision-making process to make a change feasible.

Usually, DCEs are conducted with a sample of respondents representing the “possible consumers” we intend to assess the preferences. Since the idea is to guide the implementation of recently produced science into clinical practice in Brazil, the focus groups of our experiments are supposed to be Brazilian dentists. However, important differences have been observed among different regions in Brazil [48]. Such a deal will probably be minimized since, as a multicenter study, representatives from different Brazilian regions comprise our research group. Additionally, we opted for a citizen science strategy [20], which will certainly disseminate the researchers’ action in each area and may result in a more accurate representation of different respondents’ profiles and possibly reflect different pattern preferences. Even preferences may vary from country to country; this pioneering study may produce primary information on how the scientific evidence has been adopted among health professionals and inspire adaptations to other contexts.

From a wider perspective, such methodological options may lead to findings that may feed an implementation process in a more representative, inclusive, and equitable way and, in the future, can still contribute to better outcomes for the population’s health in general.

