### Aim/Study Design

A cross-section DCE was designed to assess through the oral health professional’s perspective whether the available scientific evidence supporting a clinical alternative is considered in the decision-making process and how it is combined with other factors such as costs, patient needs, and/or dental associations or experts’ recommendations. Hypothetical situations will be created. Additionally, we intend to explore professionals’ preferences and choices associated with different interventions proposed in pediatric dentistry and supported by scientific evidence recently produced. Finally, we will check if labelling the options may influence professionals’ decisions despite the preferred attributes chosen in non-labelled alternatives. Due to these different aims, the experiment will be divided into different stages to contemplate each of the mentioned aims, and a specific DCE instrument will be designed for that.

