### Participants

Our sample will comprise Brazilian oral health professionals who agree to participate in the study. As the application will be through an online platform, those who do not have access to a device such as a smartphone, tablet, computer and/or do not have access to the internet will not be able to participate.

The recruitment strategy will target dentists from both the public and private sectors. Health Departments from different states in Brazil will be contacted as facilitators to organize an application day for the public sector. Local events (congresses and commercial meetings) will be used to recruit participants from the private sector. Participants enrolled in this study will be invited to become citizen researchers and, after a training, apply the same instrument to their peers (other dentists) in their community. This approach will be used to achieve participants from different parts of Brazil and not only those who are close to research centers [20, 21].

Participants who consent to become citizen researchers will receive training to calibrate them both in ethical aspects and methodological aspects, guaranteeing the integrity and autonomy of the participants who will be recruited by them as well as the scientific confidence and rigor of the data collected [20, 22]. Individual and collective targets will be defined for the citizens research considering the number of dentists supposed to be achieved with this strategy of citizen science. A monitoring platform will be created [23] to motivate data collection and establish communication between investigators and citizen researchers.

The sample size will be calculated based on an arbitrary rule summing up 10 respondents for each attribute defined for the DCE and extra 50 participants [24]. By anticipating a maximum of six attributes in the experiment, we expect that a sample of 110 respondents would be needed to provide sufficient statistical power based on the rule described above. An additional number of participants will be increased in sample size for compensating possible a 20% non-respondent rate, totalizing an anticipated minimum sample of 132 dentists. After defining the attributes, this calculation will be adjusted, if necessary.

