**Fig. 2 Fig2:**
[figure not shown]
Two main choice sets and hypothetical factors that potentially affect the dentists’ decision

The first one will focus on understanding the role of the attribute “scientific evidence” in the decision-making process. An experimental design will be created by combining different levels of attributes, resulting in hypothetical alternatives to measure that. The other set will focus on understanding specific attributes considered for choosing diagnostic and therapeutic interventions when such a decision is required in clinical practice. The interventions considered were related to caries diagnosis strategies and minimally invasive interventions. This set will be divided into three stages: (a) hypothetical alternatives combining levels of attributes, as the first set; (b) real alternatives, non-labelled, including the same attributes whose levels will be defined by pairs of interventions sourced by well-designed randomized controlled trials in the Brazilian context (Table 1), (c) the same alternatives from item “b”, but labelled. In this second set, the labelled and non-labelled alternatives (items “b” and “c”) will be displayed randomly to avoid generating an automatic association between them.

**Table 1 Tab1:** Newly scientific evidence. Brief description of the randomized controlled trials that will be used to guide the DCE-interventions instrument, detailing the conditions and interventions tested in each of them

NCT or REBEC (PMID)*	Condition	Age (n)	Intervention group	Control Group	Follow-up (months)	Primary outcome	Secondary outcomes
02078453 (32,450,979)	Caries lesions detection and diagnosis^**(1)**^	3–6 (252)	Visual Inspection	Visual Inspection and bite-wing radiographs.	24	Surfaces with operative treatment needed	• New carious lesion; • Repairs needed; • Pain episodes; • Extractions; • Oral health-related quality of life • Economic
02473107 ( - )	Initial carious lesions detection ^**(2)**^	3–6 (260)	Detection and treatment based on all lesions severity	Detection and treatment based on advanced carious lesions	24	Surfaces with operative treatment needed	• Economic • Discomfort • Oral health-related quality of life

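### The labelled-versus-unlabelled comparison measures a total label effect and cannot show that dentists choose on the name rather than on characteristics

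*Protocol article*

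**What the plan says.** The aim appears in two forms. Under Aim/Study Design it is neutral: "we will check if labelling the options may influence professionals’ decisions despite the preferred attributes chosen in non-labelled alternatives". In the Discussion it is sharper: the assessment is to identify possible "choice trends based on the name of the intervention rather than its characteristics". The next sentences of the Discussion turn to bias ("Different types of cognitive bias may influence decisions and difficult changes in this process"). The radiograph example in the same paragraph closes by saying that, depending on dentists' "allegiance or choice-supportive memories, they may resist change".

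The comparison that serves this aim is set out under Instrument properties, in the text after Fig. 2. Stage (b) of the second choice set presents "real alternatives, non-labelled, including the same attributes whose levels will be defined by pairs of interventions" taken from the trials in Table 1. Stage (c) presents "the same alternatives from item “b”, but labelled". The labelled and unlabelled versions are shown in random order so that respondents do not link them automatically.

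On the number of attributes, the Participants section works from an expectation: "By anticipating a maximum of six attributes in the experiment". It adds that the calculation will be adjusted, if needed, once the attributes are defined.

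**The concern.** To conclude that a choice rests on the name rather than on characteristics, nothing relevant to the choice may be left undisplayed, and respondents must accept the displayed values. A short attribute list that has to serve diagnostic strategies, materials and treatments alike is unlikely to meet the first condition, and the article describes nothing that checks the second.

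Once an intervention is named, dentists can draw on what they know or believe about it beyond the attributes shown. A dentist who changes choice at that moment may be reacting to a real feature, such as equipment, training or a professional recommendation, if that feature is not on the list. If this is read as attachment to a name, an implementation strategy could be aimed at beliefs when the obstacle is practical.

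**Working it through.** **Inputs.** The wording of the aim (Aim/Study Design; Discussion), the definitions of stages (b) and (c) (Instrument properties), the anticipated maximum of six attributes (Participants), and the outcomes listed in Table 1. The plan gives no figure for the label comparison. The six attributes enter only the sample-size rule, which reproduces: 10 × 6 + 50 = 110, and 110 × 1.2 = 132. The point here does not depend on that number.

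**Step 1: what the comparison identifies.** For one pair, let V be the utility difference carried by the displayed attributes, on the logit scale.
- Stage (b): logit P(b) = V.
- Stage (c): logit P(c) = V + N + U + D, where N is the effect of the name or of habit, U the effect of features known or believed but not displayed, and D the effect of doubt about the displayed values.
- Difference: logit P(c) − logit P(b) = N + U + D.

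There is one observable quantity and three unknowns. More respondents estimate the sum more precisely but do not separate its parts.

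**Step 2: can U be assumed to be zero?** In Table 1, the trial of visual inspection with or without radiographs lists 1 primary and 6 secondary outcomes, 7 in all. The trial comparing two sets of criteria for caries around restorations lists 1 + 7 = 8. Outcomes are not the same thing as attributes, and some could be merged, but a common list of six cannot hold every outcome of either trial separately. The article itself names further factors that may bear on decisions: training and available resources (Background), professional or expert recommendations (Aim/Study Design) and treatment complexity (Discussion). Nothing ensures that the final list covers all of these for every pair.

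**Step 3: illustrative size.** The logit values are assumptions, not trial figures. Set N = 0 and D = 0, so that there is no name effect at all, and use P = 1/(1 + e^−x).
- Even pair, V = 0, P(b) = 50%. With U = 0.5, P(c) = 62.2%. With U = 1.0, P(c) = 73.1%.
- Displayed attributes favour one option, V = 0.5, P(b) = 62.2%. With U = −0.5, −1.0 or −1.5, P(c) = 50.0%, 37.8% or 26.9%. If each respondent's random error is the same in both tasks, about 12%, 25% or 35% change their choice.
- With U = 0 the share choosing each option does not move.

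A pure name effect of the same size (N in place of U) gives exactly the same shares.

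**Step 4: individual switches.** If the random errors in the two tasks are independent and the label has no effect, the share who switch is 2P(1 − P). At P = 62.2% this is 2 × 0.622 × 0.378 = 47%, and at P = 50% it is 50%. A switch by one respondent is therefore not in itself evidence of any label effect.

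**The case against.** The strongest reply is that the operative aim is the neutral one under Aim/Study Design, and that stages (b) and (c) answer exactly that question. The Discussion sentence is hedged: the trends are possible ones, and bias may influence decisions. The remark about allegiance belongs to the radiograph example and is not offered as a rule for reading switches. The section on quantitative analysis specifies no such rule either. All of this stands. A reader might infer that every change of choice will be reported as bias; the article does not say so.

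Two further inferences would also go too far. A label does not reveal every undisplayed characteristic, only what the respondent knows or believes. Six attributes is an anticipated maximum and not a fixed limit. The attribute search and the panel, with its 80% approval threshold, are meant to capture the factors that matter, so the amount left undisplayed is not yet known. The logit values above are assumed and would apply to any labelled choice experiment.

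None of this makes the Discussion wording supportable. A good attribute list would shrink the undisplayed part, but the comparison could not show that it had vanished. Random display order deals with association between the two versions of a pair and does not touch this problem.

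**Conclusion.** The point holds as one of interpretation. Stages (b) and (c) identify a total label effect. The aim in the Discussion, of finding trends that rest on the name as opposed to the characteristics, claims more than this comparison can deliver at any sample size, and the article describes nothing that would separate the components. Choices driven by real features could be read as name-based or as bias; it is not established that they would be.

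The size in this study is unknown, because it depends on an attribute list not yet chosen. Under the assumed values, an undisplayed feature worth 0.5 to 1.0 logits shifts an even pair by 12 to 23 percentage points with no name effect. That range assumes a logit model with the same error scale in both stages; the lack of separation does not depend on these values. The neutral aim, the sample size and the rest of the experiment are unaffected.

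**What to change.** Bring the Discussion aim into line with Aim/Study Design, and carry the same wording into the analysis plan and the results report. For example: *The comparison estimates how far showing the name of an intervention changes choices between alternatives with the same displayed attributes. Any change is a total label effect: it may include what respondents know or believe about features not displayed, and doubt about the displayed values. It will not be attributed to the name alone, or to allegiance or cognitive bias.*

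This needs no change to the instrument, the sample or the model. The downside is a less specific conclusion for this aim.

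A closed question on reasons, asked after all choice tasks are finished, is at most an optional exploratory aid. It should not be used to classify switches as name-driven. It invites the after-the-fact rationalisation that the Discussion hopes to avoid by not asking directly, an answer such as usual practice or training mixes habit with a practical feature, and switches with no stated reason would include the random ones shown in step 4.

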## Data Availability

All data, including the questionnaires, all resources, and intermediate parts, will be available at https://osf.io/bhncv. The final data will be available as open data via the University of Sao Paulo online data repository.

## Abbreviations

DCE: Discrete Choice Experiment
